### Statistical analysis strategy

All statistical analyses will be performed using IBM SPSS Statistics for Windows, v.22.0 (IBM, Armonk, NY, USA). Data will be checked for normal distribution using the Shapiro-Wilk test. The primary endpoint measurement is myo-MPS. Secondary endpoints are leg lean mass (DXA), *rectus femoris* muscle thickness (ultrasound), muscle fibre CSA (immunohistochemistry) and quadriceps muscle strength (isokinetic dynamometry). All measurements will be analysed using a 2-way between and within mixed model ANCOVA with condition (ß-lactoglobulin vs. placebo) as the between-group factor and time period (basal *vs*. prehabilitation *vs.* immobilisation) as within-group factors. Diet and physical activity status will be input as covariates. Where appropriate (i.e. measurements of MPS, leg lean mass, muscle thickness and quadriceps muscle strength), a within-subject control (non-immobilised leg) will be applied to the statistical model when making between group comparisons. The key objective is to compare the effect of the intervention vs. placebo in an unpaired sample. We plan to make three comparisons between the two groups (Δ baseline to immobilisation, Δ prehabilitation to immobilisation, and Δ baseline to prehabilitation for all measurements), disregarding sex as a factor. There is a risk this may introduce type 2 error (rather than type 1 because the randomisation is granular), but we have no reason to anticipate that sex will be a significant confounder. Additional justification for this strategy is because we anticipate that the number of male and female participants will not be equal. The strategy will be to determine from the ANCOVA above whether the intervention is a significant source of variance for each of the primary and secondary endpoint measurements. Bonferroni post hoc testing will be undertaken only if *F* is significant (*P* < 0.05), and there is no variance in homogeneity. The post hoc test will be a *t* test but with an adjustment in the *P* value to accommodate the number of comparisons. The adjustment will be to add a degree of freedom for each of the comparisons. We consider this statistical approach optimal for permitting reliable discovery in a reasonable timeline. Statistical significance will be set an *α*-level of *P* < 0.05.

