## Methods/design

### Experimental design

The aim of this study is to investigate the impact of a *complex* prehabilitation intervention that combines β-lactoglobulin supplementation with resistance exercise training on disuse-induced changes in MPS, leg lean mass, muscle thickness, muscle fibre cross-sectional area and quadriceps muscle strength in healthy, young adults. To address this aim, we will conduct a parallel, double-blind, 2-arm, randomised placebo-controlled trial. An overview of the trial design is displayed in Fig. 1 and detailed in chronological order under the ‘Experimental protocol’ section. The intervention group will combine a structured resistance exercise training programme with thrice daily dietary supplementation with 23 g of β-lactoglobulin. The placebo group will combine the same training programme with an energy-matched carbohydrate (dextrose) control. The study protocol will last 16 days. Day 1 will be a familiarisation session and days 2–4 will represent the ‘baseline’ period. Days 5–11 represent the ‘prehabilitation period’ whereby participants will combine resistance training with their assigned dietary supplementation regimen. Days 12–16 represent the muscle disuse induced ‘immobilisation period’ whereby participants will have their leg immobilised in a brace for 5 days and continue their assigned dietary supplementation regimen only (i.e. no resistance training). The primary endpoint of this study is the measurement of free-living, integrated rates of muscle myofibrillar protein synthesis (myo-MPS) that will be calculated at baseline, over the 7 day prehabilitation period and the 5 day immobilisation period separately. The trial will be parallel in design given that recruited participants must be tracer naïve for the valid determination of MPS rates. Secondary endpoints include measurements of leg lean mass, muscle thickness, muscle fibre cross-sectional area and quadriceps muscle strength that will be collected at baseline (i.e. prior to intervention), after prehabilitation (day 11) and following 5 days of immobilisation (day 16).

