### Participants

To address the study objectives, a cohort of 24 healthy young (18–45 years) males and females who satisfy the inclusion and exclusion criteria outlined in Table 1 will be recruited for this trial. Eligibility will be determined using a series of self-report questionnaires and a 3-day weighed food diary to assess baseline dietary protein intake. Volunteers that report a baseline protein intake in excess of 1.2 g·kgBM^−1^·day^−1^ will be deemed ineligible for participation in this study. The protocol for this study has received ethical approval from King’s College London Research Committee (reference: HR/DP-21/22-29290) and will be conducted in accordance with the Human Tissue Act and the Declaration of Helsinki and has been registered at clinicaltrials.gov under reference number NCT05496452 (version: 1, date: 15 December 2022). Participants will be reimbursed £500 for their time invested in the study.

**Table 1 Tab1:** Inclusion and exclusion criteria

**Inclusion**	**Exclusion**
1. Male and female	1. Dairy allergy or intolerance
2. Aged 18–45 years	2. Lower limb injury or surgery in the last 6 months
3. Healthy	3. Lower limb osteoarthritis or other musculoskeletal disorder
4. Physically active (≥ 150–300 min of moderate-intensity aerobic physical activity per week OR 75–150 min of vigorous-intensity aerobic physical activity per week)	4. A musculoskeletal or blood blotting disorder
5. Eumenorrheic and not taking any hormonal birth control (females)	5. An allergy to local anaesthetic
	6. Currently pregnant
	7. Current use of blood thinning medications
	8. Volunteers that take part in structured resistance exercise training
	9. Taking supplements considered to be anabolic to skeletal muscle (protein supplements, creatine, or omega-3 supplements)
	10. Consuming more than 1.2 g of protein per kilogramme of body mass per day in their habitual diet
	11. Volunteers involved in other studies at the time of enrolment
	12. Volunteers who have taken part in a tracer study in the past 18 months
	13. If without an understanding of verbal or written English
	14. Volunteers with a history of eating disorders

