#### Diet and physical activity tracking

To assess physical activity patterns, participants will complete a three-day physical activity questionnaire and wear an Actigraph GT9X monitor (ActiGraph, Pensacola, FL, USA) for four consecutive days. These two activity monitoring techniques require participants to include two weekdays and one weekend day. This assessment will be conducted at three different time points throughout the study, once at baseline, once during the resistance exercise training period and once during the immobilisation period, in order to track changes in physical activity at different phases of the study.

The Actigraph will be secured in a pouch and worn on whichever ankle will not be immobilised. Participants will be instructed to remove the monitor during bathing, swimming, and sleeping activities but to wear it at all other times. The monitor records acceleration in three dimensions, and data will be presented as both mean vector magnitude counts per minute (VM) and time spent performing different activity levels. The threshold for these activity levels is based on a validation study for moderate and vigorous activities with this specific monitor [26], in combination with the Actigraph recommended cut point for sedentary activity [14]. Based on these studies, the cut points for sedentary, light, moderate and vigorous activity levels are < 100, 100–10,431, 10,432–19,813, and > 18,914 VM, respectively.

The physical activity questionnaire was selected from Bouchard et al. [7] as a 3-day questionnaire validated in a general population. In brief, the questionnaire requires participants to qualify the type of activity performed during each 15-min period for 72 h on a scale from 1 to 9. The scale will be discussed with participants before they are given the questionnaire. If a participant is uncertain about a particular activity, this will be discussed with a researcher to come to an agreement about the rating. The corresponding energy cost of each category was also taken from Bouchard et al. [7] and will be used to calculate total energy expenditure in METS for the three consecutive days. Dietary energy and macronutrient intake will not be strictly controlled during the trial but will be monitored by the research team to ensure background protein intake does not surpass 1.2 g•kg body mass^−1^•day^−1^.

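### Diet and physical activity enter the model as covariates without being limited to pre-intervention values; separately, the moderate and vigorous activity cut points overlap

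*Protocol article*

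**What the plan says.** The Statistical analysis strategy section of the protocol article analyses all primary and secondary measurements with a "2-way between and within mixed model ANCOVA with condition" as the between-group factor and period (basal, prehabilitation, immobilisation) as the within-group factor. It then adds: "Diet and physical activity status will be input as covariates". It does not say whether these are baseline or on-treatment values, or which diet or activity variable is meant.

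Both quantities are measured before and after supplementation starts:

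- **Activity** is assessed "once at baseline, once during the resistance exercise training period and once during the immobilisation period" (Diet and physical activity tracking).
- **Diet** is assessed at screening with "a 3-day weighed food diary to assess baseline dietary protein intake" (Participants). Later, "Dietary energy and macronutrient intake will not be strictly controlled during the trial but will be monitored by the research team", with the aim "to ensure background protein intake does not surpass 1.2" g/kg/day (Diet and physical activity tracking).

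The randomised contrast is itself dietary. The active arm has "thrice daily dietary supplementation with 23 g of β-lactoglobulin" (Experimental design), and the placebo arm has dextrose matched for energy. Both are taken through prehabilitation and immobilisation.

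The tracking section also lists vector-magnitude cut points for four activity levels. The last two, moderate and vigorous, read "10,432–19,813, and > 18,914 VM, respectively".

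**The concern.** A covariate measured before the first supplement is safe: treatment cannot have altered it, and it may improve precision. A covariate measured during supplementation is a post-randomisation variable. If treatment moves it, adjusting for it no longer estimates the effect of being assigned to β-lactoglobulin rather than dextrose. Part of the effect may be removed, and the arm term loses precision because arm and covariate carry the same information.

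That matters here because the treatment is a change in protein intake. The model has a period factor and activity is measured once per period, so period-specific covariates are a natural way to carry out the sentence, and nothing in it rules them out. With 24 participants and one undefined sentence governing the primary endpoint, the choice could range from harmless to one that removes the effect, and could be made after the data are seen.

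The cut-point overlap is a separate matter. A value in the shared band belongs to both classes, so time in moderate and in vigorous activity is not uniquely defined.

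**Working it through.** **Inputs from the protocol article.** Supplement 3 × 23 = 69 g/day; background protein cap 1.2 g/kg/day; d = 1.6; 12 per group; α = 0.05 (taken as two-sided). **Assumptions.** Body mass 70 kg (range 60 to 80 kg); within-arm SD s of on-treatment protein intake 0.2 to 0.3 g/kg/day. The article gives neither.

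**Starting point.** For a two-sample t test with 12 per group and d = 1.6, the noncentrality is 1.6 × √(12/2) = 3.92 on 22 df, and power is 0.963. (The stated inputs of d = 1.6 and power 0.80 lead to 8 per group two-sided, not 12. That is a different issue and does not affect this one.)

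**Case 1: diet covariate is total intake, supplement included.** The difference between arms is D = 69/70 = 0.986 g/kg/day. With 1:1 allocation:

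- r² between arm and covariate = 0.25D² / (0.25D² + s²), with 0.25D² = 0.243
- inflation of the SE of the arm effect = √(1/(1 − r²))
- noncentrality = 3.92 / inflation, on 21 df

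| s (g/kg/day) | r² | SE multiplied by | Noncentrality | Power at d = 1.6 |
|---|---|---|---|---|
| 0.2 | 0.243/0.283 = 0.86 | 2.66 | 1.47 | 0.29 |
| 0.3 | 0.243/0.333 = 0.73 | 1.92 | 2.04 | 0.49 |

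Over 60 to 80 kg with the same SDs, power runs from 0.23 (60 kg, s = 0.2) to 0.57 (80 kg, s = 0.3).

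These figures show loss of precision alone. A simulation adds the bias: 12 per arm, true effect 1.6, 4,000 runs, within-arm SD 15 to 25 g/day (assumed).

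| Share of effect acting through protein intake (assumed) | Mean adjusted estimate | Power |
|---|---|---|
| 0% | 1.6 | 0.30–0.56 |
| 50% | about 0.8 | 0.12–0.19 |
| 100% | about 0 | about 0.05 |

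**Case 2: diet covariate is background intake, unaffected by treatment.** In the same simulation the estimate stays at 1.59 to 1.60 and power at 0.95 to 0.96. Bias appears only if the supplement displaces habitual food. The article gives nothing from which to size that.

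**Case 3: baseline values.** These behave as in Case 2, and displacement cannot occur because they precede the first supplement.

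**Activity.** Both arms have the same training and the same brace, and allocation is blinded. A shift in activity caused by protein rather than dextrose is possible, but the article gives no reason to expect one.

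**Cut points.** Moderate ends at 19,813 and vigorous begins above 18,914. Overlap: 19,813 − 18,914 = 899 counts.

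**The case against.** The strongest reply is that the article never says on-treatment values will be used. Pre-intervention values of both covariates exist, and an article may leave their definition to a fuller document. This stands in part. A reader might infer that the plan does adjust for on-treatment intake and so removes its own treatment effect; the text does not support that. What remains is that the article does fix the adjustment, for every endpoint, in words that permit a post-randomisation covariate.

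Second, the only on-treatment diet quantity given a figure is background protein, and that wording points to leaving the supplement out. Arithmetic supports this: at an assumed 70 kg the cap is 1.2 × 70 = 84 g/day, so counting the 69 g supplement would leave 84 − 69 = 15 g/day for all food. This stands, and it makes Case 1 a worst case rather than the expected one. But the phrase describes a monitoring limit, not the covariate.

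Third, the activity mechanism is weak. This stands.

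Fourth, the cut-point overlap reaches the model only if classed activity time is the covariate. Mean vector magnitude and questionnaire energy expenditure are also collected, and neither uses the cut points. This stands too: the overlap does not show that the activity covariate is wrong. It does affect the time in each activity level that the article says will be presented.

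**Conclusion.** The point holds as a gap in a stated analysis decision, not as a demonstrated bias. Its size depends on the undefined covariate:

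- **Total on-treatment intake:** severe. Power at d = 1.6 falls from about 96% to about 29–49% (70 kg, s = 0.2 to 0.3 g/kg/day, both assumed). The estimate also shrinks in proportion to the share of the effect that acts through protein intake.
- **On-treatment background intake:** bias only if the supplement displaces habitual food; not quantifiable from the article.
- **On-treatment activity:** small risk.
- **Baseline values:** no such bias.

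The change is worth making because it costs almost nothing and protects the primary comparison. The figures for total intake should not be read as a forecast of what the trial will do.

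The cut-point contradiction is certain but minor. The two numbers look like a transposition of digits, but the article does not show which is right.

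**What to change.** In the Statistical analysis strategy section, state that only pre-intervention values enter the model: habitual protein intake (g/kg/day) from the screening food diary, and the baseline activity measurement, naming the activity variable. Report on-treatment diet, with the supplement shown separately from background intake, and on-treatment activity by arm as description. Any model that adjusts for them should be labelled as a mediation or sensitivity analysis.

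This takes one sentence and no new data, since both baseline measures are already collected. The downside is that chance differences between arms in on-treatment diet or activity are not adjusted for; the descriptive tables will show them.

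In the Diet and physical activity tracking section, check the moderate/vigorous boundary against the cited validation study and use one common value for both classes. This is one corrected number, and should be settled before activity data are classified.

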#### Power calculation

The sample size for this study has been estimated using an a priori power analysis of a previously published study by Kilroe et al. [19] that utilised the same unilateral leg immobilisation protocol, primary endpoint measurement (free-living integrated MPS rates assessed by deuterium oxide tracer methodology) and participant characteristics (healthy young adults). We calculated an effect size (d) of 1.6 for the primary endpoint (MPS) using Eq. 1.1$$\mathbf d\boldsymbol=\boldsymbol(\mathbf\mu\mathbf1\boldsymbol-\mathbf\mu\mathbf2\boldsymbol)\boldsymbol/\mathbf{SD}$$where μ1 is the mean value for muscle protein synthesis in group 1, μ2 is the mean value for muscle protein synthesis in group 2 and SD is the pooled standard deviation.

This effect size was entered into G*Power (version 3.1.9.2), with power set to 0.8 and significance level (*α*) set to 0.05. The required sample size was projected to be 12 per group, for a total of 24 participants. Hence, we plan to recruit 24 healthy, young (18–45 years) males and females from the local area. Recruitment will proceed on a rolling basis until the adequate sample size is reached. Emphasis will be placed on considering the demands of the study before enrolment to minimise loss to follow-up.

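### The F test that gates the between-arm comparisons is, read literally, a condition main effect averaged over the untreated baseline; the matching condition-by-time interaction is never named

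*Protocol article*

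**What the plan says.** The Statistical analysis strategy section of the protocol article sets a two-way mixed ANCOVA with condition (β-lactoglobulin or placebo) "as the between-group factor and time period" (basal, prehabilitation, immobilisation) as the within-group factor. Diet and physical activity are covariates, and the non-immobilised leg serves as a within-subject control where available.

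Three between-arm comparisons are planned, each of a change: baseline to immobilisation, prehabilitation to immobilisation, and baseline to prehabilitation. The order of testing is fixed. The analyst is first to "determine from the ANCOVA above whether the intervention is a significant source of variance for each of the primary and secondary endpoint measurements". Then "Bonferroni post hoc testing will be undertaken only if" F is significant at P < 0.05. The text does not say which F is meant.

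Under Prehabilitation period, the supplement is given throughout prehabilitation and immobilisation, so the baseline period is untreated in both arms. The first objective, at the end of the Background, concerns the fall in integrated MPS during disuse.

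**The concern.** The intervention is the condition factor. Asking whether it is a significant source of variance is, on the plain words, asking for the condition main effect. In a design with three time levels, that effect compares the arms on the mean of the three periods. Three problems follow.

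- One of the averaged periods precedes any supplement and cannot show an effect, so it dilutes the signal.
- A chance baseline difference between the arms is averaged in. The change comparisons would subtract it.
- All three planned comparisons are differences in change, that is, condition-by-time contrasts. The main effect tests a different quantity, so it can block a comparison that would itself have been significant.

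At stake is whether the comparison that answers the first objective is made at all. The rule also covers every secondary endpoint. Because the document states the rule, this is more than a detail left to a fuller analysis plan.

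**Working it through.** **Inputs from the protocol (Power calculation).** "We calculated an effect size (d) of 1.6 for the primary endpoint (MPS"), defined as a difference between two group means where "SD is the pooled standard deviation"; power 0.8; α 0.05; 12 per group.

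**The plan's own figure.** A two-sided two-sample t test at d = 1.6 and α = 0.05 reaches 80% power with 8 per group, and 12 per group gives 96%. The stated 12 does not follow from the stated inputs. That is a separate matter; here 12 per arm is simply the planned size.

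**Assumptions not in the document.** Equal SD in each period; one common between-period correlation ρ, varied from 0 to 0.9; two-sided tests; covariates and the control leg left out; d = 1.6 taken as the arm difference within a single period.

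**Formulas, with 12 per arm.**

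- Main effect: d_main = (sum of period effects / 3) / √((1 + 2ρ)/3); noncentral t, 22 df, noncentrality d_main × √6.
- Interaction: noncentral F with 2 and 44 df, λ = 6 × Σ(period effect − mean effect)² / (1 − ρ).
- Direct test of the baseline-to-immobilisation change: d_change = 1.6 / √(2(1 − ρ)); noncentral t, 22 df.

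**Worked case: effect in immobilisation only, ρ = 0.5.**

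- Main effect: (1.6/3)/√(2/3) = 0.533/0.816 = 0.653; noncentrality 0.653 × 2.449 = 1.60; power 33%.
- Interaction: the effects 0, 0, 1.6 have mean 0.533 and squared deviations summing to 1.707; λ = 6 × 1.707/0.5 = 20.5; power 98%.
- Direct change: 1.6/√1 = 1.6; power 96% at 0.05 and 90% at 0.05/3.

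**Probability that the gate opens.** Effects are listed as baseline, prehabilitation, immobilisation.

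| Effects (d) | Gate | ρ = 0 | 0.3 | 0.5 | 0.7 | 0.9 |
|---|---|---|---|---|---|---|
| 0, 0, 1.6 | main effect | 58% | 40% | 33% | 29% | 25% |
| 0, 0, 1.6 | interaction | 80% | 92% | 98% | >99% | >99% |
| 0, 0.8, 1.6 | main effect | 90% | 73% | 63% | 55% | 49% |
| 0, 0.8, 1.6 | interaction | 67% | 83% | 93% | >99% | >99% |
| 0, 1.6, 1.6 | main effect | 99% | 93% | 86% | 80% | 73% |
| 0, 1.6, 1.6 | interaction | 80% | 92% | 98% | >99% | >99% |

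The direct change test does not depend on the prehabilitation effect. Its power at 0.05 is 75%, 89%, 96% and 99.8% at ρ = 0, 0.3, 0.5 and 0.7. At 0.05/3 it is 58%, 76%, 90% and 99%.

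**Gate and contrast together.** Under these assumptions the three-period mean is uncorrelated with a change score, so the two-step success rate is close to the product. For immobilisation only at ρ = 0.5 this is 0.334 × 0.897 = 0.30. Simulation of 20,000 trials gave 30% to 31%, and 28% to 29% at ρ = 0.7.

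**The case against.** The strongest reply is that the text never says main effect. It says only F, in a two-way between/within design, and then lists three comparisons of change. An analyst could reasonably take the interaction F as intended, and most of the loss then disappears. This stands: the wording does not settle which F is meant. It does not remove the point, because the literal subject of the sentence is the intervention and the two readings can lead to very different analyses.

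A reader might also infer that the primary comparison has only about a 3 in 10 chance of being made. The documents do not support that as a general statement. It needs the main-effect reading, an assumed correlation of about 0.5 to 0.8, and an effect confined to immobilisation. The supplement is also given during prehabilitation, and the Background describes amino acids and resistance exercise as additive, so an arm difference in that period is plausible. With effects in both periods and low correlation, the main effect can open the gate more often than the interaction does.

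Nor does the calculation show that the design falls short of 80% power. The correlation, covariates and control leg are not quantified in the document, and the sample-size figure has its own discrepancy.

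Finally, a preliminary F is conventional and does not inflate type I error. That is correct. The harm is lost power and an unclear rule.

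**Conclusion.** The point holds as a badly fixed rule, not as a demonstrated power failure. Read literally, the gate is a main effect averaged over an untreated period, which is the wrong test to stand in front of contrasts of change; the test that matches them is not named.

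With 12 per arm, equal SDs, a common correlation from 0 to 0.9, and covariates and control leg ignored, a main-effect gate opens in 58% down to 25% of trials if d = 1.6 occurs in immobilisation only. The range is 90% to 49% with a further d = 0.8 in prehabilitation, and 99% to 73% with d = 1.6 in both periods. An interaction gate opens in about 80% at ρ = 0 and 92% or more from ρ = 0.3 in the first and third patterns; in the middle pattern it opens in 67% at ρ = 0, 83% at 0.3 and 93% at 0.5.

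The choice of F should not be left to someone who can see the data.

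**What to change.** Amend the Statistical analysis strategy before unblinding, in one of two ways.

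- **Minimum.** State that the F that must be significant before the between-arm comparisons is the condition-by-time interaction, not the condition main effect.
- **Preferred.** Prespecify the between-arm difference in baseline-to-immobilisation change in myo-MPS as the primary contrast. Test it directly at two-sided 0.05 with no preliminary main-effect F, keeping the planned covariates and control-leg term. If all three contrasts are to rank equally, test each at 0.05/3. The adjustment now described, adding a degree of freedom per comparison, is not a Bonferroni correction.

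The cost is a few sentences, with no further data, visits or participants. With a single primary contrast, the other two comparisons become secondary. With three equal contrasts, power for each is lower: at ρ = 0.5, 90% instead of 96% under the assumptions above.

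### The planned between-arm change comparisons may be run only if variances are homogeneous; unequal spread would leave them untested, although valid tests do not need that condition

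*Protocol article*

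**What the plan says.** The Statistical analysis strategy section sets out three steps.

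- **Overall test.** A mixed ANCOVA with condition as the between-group factor and time period as the within-group factor: "The strategy will be to determine from the ANCOVA above whether the intervention is a significant source of variance" for each primary and secondary endpoint. This step is not made conditional on homogeneity.
- **Planned comparisons.** The section states that "The key objective is to compare the effect of the intervention vs. placebo in an unpaired sample" and that "We plan to make three comparisons between the two groups": change from baseline to immobilisation, from prehabilitation to immobilisation, and from baseline to prehabilitation, for every measurement.
- **Rule for carrying them out.** "Bonferroni post hoc testing will be undertaken only if *F* is significant (*P* < 0.05), and there is no variance in homogeneity". The test itself is then described: "The post hoc test will be a *t* test but with an adjustment in the *P* value to accommodate the number of comparisons".

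The section names no homogeneity test or threshold and does not say which variances are to be compared. It gives no alternative if the condition fails. On size, the Power calculation section says "The required sample size was projected to be 12 per group, for a total of 24 participants", using d = 1.6, power 0.8 and α 0.05. The Randomisation process section gives 1:1 allocation.

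**The concern.** Taken literally, the closing phrase of the rule is not a usable condition. Read as no inhomogeneity of variance, it makes a comparison of means depend on the outcome of a check on spread. Whether the arms have equal variance is a different question from whether mean change differs between them.

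The first objective in the Background asks whether the intervention attenuates the fall in MPS during disuse. That is a question about a particular change, and the change comparisons sit behind the condition. If F is significant but the arms differ in spread, the rule as written stops there, for myo-MPS as for every other endpoint. The overall F does not say which change differs. The power calculation makes no allowance for this.

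The condition would be defensible if the comparison were invalid without it. The check below asks whether it is, and what the condition costs.

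**Working it through.** **Inputs from the article.** 12 per arm, 1:1 allocation, d = 1.6 where "SD is the pooled standard deviation", power 0.8, α 0.05, three between-arm comparisons.

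**Assumptions (not in the article).** Two-sided testing; normal data; Levene's test (mean-centred) at 5% as the homogeneity check; SD ratio r between arms from 1 to 3. The requirement of a significant F and the covariates are left out, so the figures isolate the variance condition.

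**Step 1: the plan's own figure.** The normal approximation gives n = 2(1.96 + 0.84)²/1.6² = 6.1, so 7 per arm. The exact t calculation gives 7.23, so 8 per arm. The stated 12 per group is therefore not reproduced from d = 1.6 and power 0.8. That is a separate matter; 12 per arm is used here as stated. At 12 per arm the noncentrality is 1.6 × √(12/2) = 3.92 on 22 degrees of freedom, and power is 96.3%.

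**Step 2: simulation.** 12 v 12, 100,000 runs per scenario. The arm SDs are 1/k and r/k with k = √((1 + r²)/2), so the pooled SD stays at 1 and d keeps its meaning. The conditional result counts a trial only if Levene's test is non-significant and the pooled t test is significant.

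| SD ratio | Blocked by Levene | Power, no condition (pooled t) | Power, no condition (Welch) | Power with condition (pooled t) |
|---|---|---|---|---|
| 1 | 5.9% | 96.3% | 96.3% | 90.6% |
| 1.5 | 22.1% | 96.1% | 95.9% | 75.2% |
| 2 | 50.1% | 96.1% | 95.6% | 48.5% |
| 3 | 84.8% | 96.0% | 95.2% | 14.9% |

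The loss is essentially the blocking rate. At ratio 1, 0.963 × (1 − 0.059) = 0.906. At ratio 2, 0.961 × (1 − 0.501) = 0.480, against 0.485 simulated.

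The median-centred form of Levene's test blocks less often: 3.7%, 16%, 40% and 77% at the same four ratios.

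**Step 3: with a Bonferroni level.** At 0.05/3 the pooled t test without the condition has power 89.6%, 89.7% and 89.5% at ratios 1, 1.5 and 2. With the condition it is 84.4%, 70.5% and 46.0%.

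**Step 4: what the condition protects against.** With no mean difference and 12 v 12, the pooled t test without the condition rejects in 5.0%, 5.2%, 5.4% and 5.8% of trials at ratios 1, 1.5, 2 and 3. Welch rejects in 4.9% to 5.1%. With uneven arms (9 v 12, SD ratio 2, larger SD in the smaller arm) the pooled t test rejects in about 7.8% without the condition and 5.1% with it. Welch rejects in about 5.0% without any condition.

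**The case against.** **The main analysis survives.** A reader might infer that unequal variances cost the trial its primary analysis, or that any positive result must first pass a variance check. The article does not support that. The condition attaches to the post hoc tests; the ANCOVA F for the intervention comes earlier and is free of it. This stands, and it limits the point to the change contrasts. The loss still matters, because the section makes the between-group comparison its key objective and the first objective concerns a particular change.

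**The wording is garbled.** The homogeneity reading is an interpretation, and Levene at 5% is supplied here. This stands as a limit on the figures. It does not rescue the rule: if that reading is refused, the condition on the planned comparisons cannot be applied at all and must be rewritten anyway.

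**A fallback may be in the analysis plan.** What to do when an assumption fails is often left there, so its absence from an article carries little weight alone. The objection here is to a stated rule. An analysis plan that ran the contrasts despite inhomogeneity would contradict the "only if" in the article.

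**The large losses need large SD ratios.** The article gives no SD ratio. With equal spread the cost is about 6 points, and power stays above the 80% target. A reader might also infer that the supplement will widen the spread in the active arm, so that a real effect blocks its own test. That is possible, but nothing in the article reports it.

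**The condition is not wholly idle.** If dropout leaves uneven arms, it reins in the pooled t test somewhat. This is correct, but Welch achieves the same control without blocking any comparison.

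**Conclusion.** The point holds for the three planned change comparisons, not for the ANCOVA F. As written, a significant F with unequal spread leaves untested the contrasts that address the first objective. On the assumptions above (12 v 12, d = 1.6, Levene at 5%, two-sided 0.05), the chance of an allowed and significant contrast falls from about 96% to about 91%, 75% and 48% at SD ratios 1, 1.5 and 2. The true ratio and the intended check are unknown, so these figures are a range and not a forecast. In return, with equal arms, the condition offers almost no type I error protection. With uneven arms it gives some to the pooled t test, but Welch does not need it. The interpretation of the garbled phrase is the main uncertainty; under any reading the sentence needs correcting.

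**What to change.** In the Statistical analysis strategy section, delete the homogeneity phrase as a prerequisite for the planned contrasts. State that the between-arm comparisons of change will be carried out, whatever the homogeneity check shows, with a method valid under unequal variances: a Welch t test on change scores, or a mixed model with arm-specific residual variances. Report the homogeneity check descriptively.

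The cost is a sentence or two of text, with no extra data or participants. If variances are in fact equal and the arms are 12 v 12, Welch gives up about 0.1 point of power at d = 1.6 and two-sided 0.05 (96.32% v 96.25%), and about 0.3 points at 0.05/3 (89.6% v 89.2%).
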